### 2.5. Data Analysis

Descriptive statistics of participants’ demographic information and measures will be conducted. We will summarize the statistic of the number of study participants who achieve the feasibility endpoint over the total study sample size (N = 60), i.e., a percentage statistic. Any study participant who completes at least 4 out of 6 assessments during the study will be considered as reaching the feasibility endpoint. It is possible that a study participant may complete the EH Voice Tool more frequently than designed, e.g., completing EH Voice Tool more than once per month, leading to a total number of assessments greater than 6 times over the 6 month study period. These participants will be viewed the same as those who complete 4–6 assessments during the study period. In addition, we will also report descriptive statistics for the Acceptability of Intervention Measure, i.e., mean and standard deviation, to quantify the participants’ perceived EH Voice Tool acceptability.

We will also explore if AYA cancer patients’ D&A scores (measured via the EH Voice Tool) differ by a patient’s current stage of pivotal timepoint, i.e., 2–4 weeks after a new diagnosis, within 2 weeks of (new) treatment (including changes in planned treatment), during the transition to survivorship care (2–4 weeks finishing treatment), and one year after the completion of treatment. For this analysis, we will conduct a one-way between group analysis of variance (ANOVA) with the PHQ-8 and GAD-7 at each timepoint as the (continuous) dependent variable and the 4 pivotal treatment timepoints as the grouping variable. In addition, we will also explore if the change in the PHQ-8 and GAD-7 scores over time, i.e., over the 6 times, differ by the 4 pivotal timepoints through latent growth curve modeling. We understand that our planned sample size of 60 participants may not provide sufficient power and regard this analysis only as exploratory.

Qualitative interview data with AYA cancer patients (*n* = 15) and oncologists (*n* = 10) will first be transcribed verbatim and coded using thematic content analysis in NVivo 12 (QSR International Pty Ltd., 2018, https://www.qsrinternational.com/nvivo-qualitative-data-analysis-software/home, accessed on 16 December 2021), with discrepancies resolved through discussion. Axial code mapping will organize data into higher categories of themes related to the EH Voice Tool’s acceptability: (1) participants’ and oncologists’ perceived acceptability, (2) participants’ and oncologists’ perceived strengths and weaknesses of EH Voice Tool, (3) participants’ and oncologists’ perceived facilitators of EH Voice Tool uptake, and (4) participants’ and oncologists’ perceived barriers of EH Voice Tool.

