**Abstract:**

Adolescents and young adults (AYAs) diagnosed with cancer are an age-defined population, with studies reporting up to 45% of the population experiencing psychological distress. Although it is essential to screen and monitor for psychological distress throughout AYAs’ cancer journeys, many cancer centers fail to effectively implement distress screening protocols largely due to busy clinical workflow and survey fatigue. Recent advances in mobile technology and speech science have enabled flexible and engaging methods to monitor psychological distress. However, patient-centered research focusing on these methods’ feasibility and acceptability remains lacking. Therefore, in this project, we aim to evaluate the feasibility and acceptability of an artificial intelligence (AI)-enabled and speech-based mobile application to monitor psychological distress among AYAs diagnosed with cancer. We use a single-arm prospective cohort design with a stratified sampling strategy. We aim to recruit 60 AYAs diagnosed with cancer and to monitor their psychological distress using an AI-enabled speech-based distress monitoring tool over a 6 month period. The primary feasibility endpoint of this study is defined by the number of participants completing four out of six monthly distress assessments, and the acceptability endpoint is defined both quantitatively using the acceptability of intervention measure and qualitatively using semi-structured interviews.

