### 2.3. Participant Recruitment and Study Procedures

AYA cancer survivors will be recruited at the University of Michigan Rogel Cancer Center, C.S. Mott Children’s Hospital Division of Hematology/Oncology, and the Michigan Medicine AYA Oncology Program. Recruitment will occur over 12 months to maximize sample size. Two trained research staff (RS) will visit the outpatient and inpatient clinics at C.S. Mott Children’s Hospital Division of Hematology/Oncology and the Sarcoma Clinic at Rogel Cancer Center when the patients are waiting for their appointments. We will also work closely with the patient navigator of the Michigan Medicine AYA Oncology Program to promote study recruitment and enrollment. In addition to active recruitment, study investigators ([name] and [name]) will share the study with their colleague pediatric oncologists and encourage them to refer participants to the study.

Upon successful recruitment, a trained RS will schedule an initial meeting (T0) to obtain consent/assent and conduct a baseline assessment. The RS will also provide instructions for using EH Voice Tool. A participant will be asked to use EH Voice Tool once a month for 6 months, i.e., a total of 6 times (T1–T6). Participants will receive phone-based notifications once a month reminding them about using the mobile app. If a participant misses a scheduled assessment, the mobile app will send two more notifications 24 and 48 h after. Participants adherence to the EH Voice Tool will be monitored using the platform administrative data of each participant’s usage of the tool, e.g., how many times a participant used the app and for how long each time. By the end of month 6, the RS will meet with all participants for a brief post-study assessment (T7). Table 2 describes all measures and the time of measure administration for the study. Finally, the RS will reach out to a subsample of participants (*n* = 15), including 10 participants who achieve the feasibility endpoint (defined later) and 5 who do not achieve the feasibility endpoint and conduct semi-structured qualitative interviews to evaluate participants’ perceived feasibility and acceptability of the EH Voice Tool, and identify facilitators and barriers associated with EH Voice Tool uptake.

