### 2.4. Study Endpoints

The primary feasibility endpoint will be measured by the observed number of times each participant completes the EH Voice Tool out of the total possible times completing the tool, i.e., 6 times. If a participant completes the EH Voice Tool 4 or more times during a 6 month period, i.e., ≥66.66% rate of completion, that participant is regarded as achieving the feasibility endpoint. This feasibility study will be considered as successful if 60% or more of the participants, i.e., ≥36, reach the feasibility endpoint. The 60% benchmark for success was selected based on a national study reporting a 53% completion rate of one-time distress screening among U.S. cancer patients [18]. Therefore, we consider a 60% multiple-time (versus one-time) distress monitoring compliance rate being superior to the current practice of distress screening.

The secondary acceptability endpoint will be measured by the Acceptability of Intervention Measure, which is a psychometrically validated implementation scale that specifically measures treatment acceptability. An average score of 4.0/5.0 will be considered as evidence of EH Voice Tool acceptability.

We will also collect demographic information of all participants via self-report, which will include patient age, sex, gender identity, and race/ethnicity. Clinical information abstracted directly from patient electronic health records (EHRs) will include cancer diagnosis, prescribed therapy, and staging of disease. During the baseline assessment, we will evaluate a participant’s general mental status using the MINI interview; depression using the Patient Health Questionnaire, 8 items (PHQ-8); and anxiety using the Generalized Anxiety Disorder, 7 items (GAD-7).

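### The primary endpoint is defined both as four of six monthly assessments and as four or more uses in six months; the count version can inflate the feasibility rate

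*Protocol article*

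**What the plan says.** The protocol article describes the endpoint in two ways.

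**By month.** The abstract gives it as "the number of participants completing four out of six monthly distress assessments". Section 2.3 plans one use per month for six months, labelled T1 to T6, with two further reminders after a missed assessment.

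**By count.** Section 2.4 measures completions "out of the total possible times completing the tool, i.e., 6 times", and sets the individual threshold this way: "If a participant completes the EH Voice Tool 4 or more times during a 6 month period, i.e., ≥66.66% rate of completion". Section 2.5 first repeats the threshold as at least four of six. It then anticipates participants "completing EH Voice Tool more than once per month, leading to a total number of assessments greater than 6 times", and settles their status: "These participants will be viewed the same as those who complete 4–6 assessments during the study period". Section 2.6 repeats four of six without saying whether these are scheduled occasions.

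No section limits the count to one per month or asks for four different months. The study succeeds if at least 36 of 60 participants (60%) reach the endpoint.

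**The concern.** The two definitions agree only for participants who never record more than once in a month. For the others, the count rule can award success without four monthly assessments, and the 66.66% figure is then no longer a share of six scheduled occasions.

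This matters because the study is about monitoring over time. The introduction criticises screening done only once, and section 2.4 supports the 60% benchmark by contrasting repeated monitoring with a 53% rate for one-time screening. A burst of early use followed by silence is not repeated monitoring in that sense. Extra use is plausible: section 1.2 says the app usually returns a score within a minute and displays past trends.

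The endpoint also decides who is interviewed as an achiever (10 participants) or a non-achiever (5), so an early-burst user who disengaged could be interviewed as a success.

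**Working it through.** **1. The plan's own figures.** 0.60 × 60 = 36 and 4/6 = 0.6667. Both reproduce. The issue is what is counted, not the thresholds.

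**2. Usage patterns under each definition**

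| Pattern | Monthly definition (abstract, 2.3) | Count definition (2.4, 2.5) |
|---|---|---|
| One recording in each of 4 months | 4 of 6: reached | 4 uses: reached |
| 4 recordings in month 1, none later | 1 of 6: not reached | reached, on the literal wording of 2.4 |
| 7 recordings in month 1, none later | 1 of 6 (16.7%): not reached | reached, by the handling sentence in 2.5 |

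**3. Direction.** Let K be the number of distinct months with a completion and N the total number of completions. N is never less than K, so everyone with K ≥ 4 also has N ≥ 4. The difference between the two rates is P(K ≤ 3 and N ≥ 4), which is zero or positive.

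**4. Size with independent months.** The article gives neither a monthly completion rate (p) nor a repeat-use rate (q), so both are assumptions. Take K ~ Binomial(6, p), and let each active month bring exactly one extra recording with probability q. With at most one extra per month, only K = 2 and K = 3 can be lifted to four uses:

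shift = P(K=2) × q² + P(K=3) × [1 − (1 − q)³]

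Example, p = 0.55 and q = 0.20:
- P(K=2) = 15 × 0.55² × 0.45⁴ = 0.1861
- P(K=3) = 20 × 0.55³ × 0.45³ = 0.3032
- shift = 0.1861 × 0.04 + 0.3032 × 0.488 = 0.0074 + 0.1480 = 0.155
- P(K ≥ 4) = 0.442, so the count rate is 0.442 + 0.155 = 0.597

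The chance of study success is P(Binomial(60, rate) ≥ 36).

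| p | q | Monthly rate | Count rate | Shift (points) | P(≥36/60), monthly | P(≥36/60), count |
|---|---|---|---|---|---|---|
| 0.50 | 0.10 | 34.4% | 43.1% | 8.7 | 0.000 | 0.006 |
| 0.50 | 0.20 | 34.4% | 50.6% | 16.2 | 0.000 | 0.09 |
| 0.55 | 0.05 | 44.2% | 48.5% | 4.4 | 0.01 | 0.05 |
| 0.55 | 0.10 | 44.2% | 52.6% | 8.4 | 0.01 | 0.15 |
| 0.55 | 0.20 | 44.2% | 59.7% | 15.5 | 0.01 | 0.54 |
| 0.60 | 0.05 | 54.4% | 58.4% | 4.0 | 0.23 | 0.46 |
| 0.60 | 0.10 | 54.4% | 62.1% | 7.6 | 0.23 | 0.68 |
| 0.60 | 0.20 | 54.4% | 68.5% | 14.0 | 0.23 | 0.94 |
| 0.70 | 0.10 | 74.4% | 79.5% | 5.1 | 0.995 | about 1.00 |

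(Shifts were taken before rounding.)

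**5. Size when adherence varies between participants.** Replace the binomial for K by a beta-binomial with mean 0.55 and a + b = 1 or 2 (assumed), keeping q = 0.20. Fewer participants then sit at two or three months.
- a + b = 1: P(K=2) = 0.0980 and P(K=3) = 0.0965. Shift = 0.0980 × 0.04 + 0.0965 × 0.488 = 0.051. The rate goes from 51% to 56%, and P(≥36/60) from 0.10 to 0.30.
- a + b = 2: P(K=2) = 0.1330 and P(K=3) = 0.1409. Shift = 0.1330 × 0.04 + 0.1409 × 0.488 = 0.074. The rate goes from 49% to 57%, and P(≥36/60) from 0.06 to 0.34.

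At q = 0.05, where 1 − 0.95³ = 0.1426, the same formula gives 0.0980 × 0.0025 + 0.0965 × 0.1426 = 0.014 and 0.1330 × 0.0025 + 0.1409 × 0.1426 = 0.020.

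**6. Limit of the model.** It allows one extra recording per active month, so it does not contain bursts such as seven in one month. Extra use concentrated among participants who stop early would enlarge the shift. The article gives no information on this.

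**The case against.** The strongest reply is that most of the article points to scheduled occasions: the abstract says monthly, section 2.3 lists T1 to T6, section 2.4 names six possible times, and sections 2.5 and 2.6 repeat four of six. On that view only the handling of extra uses is badly worded. The sentence in 2.5 literally covers totals above six, and it can be read as a cap that gives heavy users no extra credit.

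Much of this stands. A reader might infer that 2.5 expressly credits someone with four early recordings. It does not; that case qualifies only through the literal wording of 2.4. But the reply does not remove the conflict. Section 2.4 sets the threshold as a number of times with no monthly limit, and 2.5 puts participants with more than six uses on a par with those at four to six without checking months.

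It is also fair that results near the 60% cut-off exaggerate the practical effect, and that independent months enlarge it. The ranges above therefore include scenarios where the decision does not change and a model with varying adherence.

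Finally, a count of four completions is a defensible measure of repeated use in a single-arm pilot. It is still a different endpoint from the one in the abstract, and the plan should state which one decides success.

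**Conclusion.** The primary endpoint is defined inconsistently, and the count version can credit clustered use as sustained monitoring. The direction is certain: the count-based rate equals or exceeds the monthly rate.

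The size is not known. At assumed mean monthly completion of 0.55–0.60 and a 5–20% chance of an extra recording per active month, the shift is about 4–16 points with independent months. With varying adherence it is about 5–7 points at mean 0.55 and 20%, and less at lower repeat use. For scale, the gap between the 53% reference and the 60% benchmark is 7 points.

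The choice of rule can change the 36-of-60 decision when the true rate is near 60%. It matters little when the rate is far away: at p = 0.70 success is near certain either way, and at p = 0.50 with q = 0.10 failure is near certain either way.

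A reader might conclude that the reported rate will be inflated. The article does not support that, because it gives no repeat-use rate and the effect could be nil.

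**What to change.** In sections 2.4 and 2.5, define the endpoint as at least one completed recording in at least 4 of the 6 monthly windows (T1–T6), counting at most one completion per window. Replace the sentence on participants with more than six uses accordingly. Keep the 36-of-60 threshold and the sample size, and report total uses as a separate descriptive. Apply the same definition when selecting achievers and non-achievers for interview.

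The change is mainly one of wording, but it has costs. Each window needs a start, a length and a rule for late completions. The sponsor should confirm that the platform data carry the date of each use: section 2.3 mentions the number and duration of uses but not dates, although the trend displays in section 1.2 suggest dates exist. The observed rate may also be somewhat lower than under the count rule.

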Three key factors contribute to poor distress screening and monitoring among AYA cancer survivors. First, oncologists and other providers do not have time and often lack the expertise to accurately assess and intervene for psychological distress. For example, 40% of oncologists find routine distress screening impractical and 56% of providers are unsure of the clinical interpretation of distress measures [20,21]. Second, AYA cancer survivors are the least likely group to disclose symptoms of psychological distress in comparison to adult patients due to emotional burden or by their desire not to worry family members [22,23]. Studies have consistently documented the emotional burden and maladaptive coping behaviors among AYA cancer survivors experiencing psychological distress, such as self-isolation and social withdrawal [24]. Finally, even for cancer centers that successfully implement distress screening protocols, most assessments are one-time efforts and do not longitudinally monitor the trajectory of psychological distress. This is problematic because AYA cancer survivors’ distress trajectories fluctuate over time, and it is critical to monitor patients’ distress throughout their cancer journey [25,26], especially during pivotal treatment time points.

Studies have documented four pivotal time points when the risk of clinical distress peaks throughout a patient’s cancer journey: 2–4 weeks after a new diagnosis, within 2 weeks of starting or changing to new treatment (e.g., chemotherapy to bone marrow transplant), during the transition from active treatment with a curative intention to post-treatment survivorship care (2–4 weeks after finishing treatment), and one year post-treatment [25,27]. Taken together, it is crucial to create and evaluate innovative methods that are flexible, engaging, and effective in monitoring psychological distress among AYA cancer survivors over time. Recent advances in speech-based distress assessment and AI have provided promising solutions to the aforementioned challenges.

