## Figures and Tables

**Figure 1 cancers-14-00914-f001:**
[figure not shown]

[figure not shown]
EH Voice Tool mobile app user interface. (**A**) voice collection, (**B**) numeric results, (**C**) visual results, (**D**) trend over time option 1, (**E**) trend over time option 2, (**F**) resource center.

**Table 1 cancers-14-00914-t001:** Clustered recruitment strategy.

Recruitment Clusters	ND	CT	ET	PT	Total
Male Adolescent (15–17 years)	4	4	4	4	16
Female Adolescent (15–17 years)	4	4	4	4	16
Male emerging adult (18–26 years)	4	4	3	3	14
Female emerging adult (18–26 years)	4	4	3	3	14
Total	16	16	14	14	60

ND = newly diagnosed; CT = change in treatment; ET = end of therapy; PT = one-year post treatment.

**Table 2 cancers-14-00914-t002:** Study measures and assessment time points *.

Measure	Measure Administration Time Points and Personnel			
	T0	T1–T6	T7	Admin
MINI Interview	X			RS
PHQ-8	X			RS
GAD-7	X			RS
EH Voice Tool Admin. Data		Ongoing all participants		Platform
AIM Measure			X	RS
Qualitative Interview			X	RS

* MINI Interview = Mini-International Neuropsychiatric Interview; PHQ-8 = Patient Health Questionnaire, 8-item; GAD-7 = Generalized Anxiety Disorder, 7-item; EH Voice Tool Admin. Data = EH Voice Tool Back Stage Administrative Data; AIM Measure = Acceptability of Intervention Measure; RS = research staff; Platform = platform-based data administration.

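### The exploratory stage analysis is worded as a comparison by current pivotal stage, but with stage set at recruitment and monthly scores it can describe only stage at enrolment

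*Protocol article*

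**What the plan says.** Section 2.5 (Data Analysis) asks whether scores obtained from the voice tool "differ by a patient’s current stage of pivotal timepoint, i.e., 2–4 weeks after a new diagnosis, within 2 weeks of (new) treatment". The list continues with "during the transition to survivorship care (2–4 weeks finishing treatment), and one year after the completion of treatment". The method is a one-way between-group ANOVA "with the PHQ-8 and GAD-7 at each timepoint as the (continuous) dependent variable and the 4 pivotal treatment timepoints as the grouping variable". A second analysis asks whether change in the scores "over the 6 times, differ by the 4 pivotal timepoints through latent growth curve modeling". The section calls this work exploratory and gives limited power as the reason.

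Three other places bear on the grouping:

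- **Section 2.2 and Table 1** use the pivotal timepoints, with age and sex, as stratifying factors for recruitment. Each participant is placed once, in one cell.
- **Section 2.3** sets the schedule: "A participant will be asked to use EH Voice Tool once a month for 6 months" (T1–T6), after a baseline meeting (T0). The interval from T0 to T1 is not given.
- **The treatment stage is described differently in different places.** The Introduction has "within 2 weeks of starting or changing to new treatment", and Section 2.5 likewise refers to new treatment and includes changes in planned treatment. The Table 1 footnote has "CT = change in treatment".

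Table 2 schedules the PHQ-8 and GAD-7 questionnaires at T0 only. The repeated scores in Section 2.5 must therefore be the tool's predictions of them.

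**The concern.** A stage fixed at recruitment and a stage current at each assessment are different variables. Three of the four stages are short windows, and the scores are collected over six months. Someone recruited shortly after diagnosis will soon leave that window and may later change or finish treatment.

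The article does not say which variable defines the groups, and the wording fails on either choice:

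- If the group is the recruitment stratum, most of the comparisons are not by current stage.
- If stage is re-read at each assessment, entry windows have closed, participants may fit no group, and some may move to another. A fixed-group growth model does not describe such movement.

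The stake is interpretation. The Introduction motivates the tool by distress peaking in these windows, and the Discussion says the findings will inform a larger trial. A flat result could be read as no difference between stages when few or no participants were in the stage named. The stated caveat about power does not cover this, because more participants would not cure it.

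**Working it through.** **Inputs**

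- Planned strata (Table 1): newly diagnosed (ND) 16, change in treatment (CT) 16, end of therapy (ET) 14, one year post-treatment (PT) 14.
- Window widths (Introduction, Section 2.5): ND and ET run from week 2 to week 4, so 14 days. CT is 14 days if counted after the start or change, and 28 days if read as two weeks either side. PT has no stated width and is left out.
- Spacing: monthly, taken as 30.4 days (assumption).
- Lag from stratum entry to T1: not stated, so varied over 0, 7, 14 and 30.4 days.
- Entry spread evenly over the window (assumption).

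**Step 1. Table 1 totals.** 16 + 16 + 14 + 14 = 60, as printed. Grouped by stage at enrolment, these are the group sizes at every assessment before missed assessments.

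**Step 2. Assessments per window.** 14 < 30.4 and 28 < 30.4, so two scheduled assessments cannot fall in the same window. T2 comes at least 30.4 days after entry, so from T2 on the share of ND, CT or ET participants still in the entry window is 0%.

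**Step 3. Share in the entry window at T1.** For width w and lag L, the share is max(0, 1 − L/w).

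| Lag L (days) | w = 14 (ND, ET, CT) | w = 28 (CT, two weeks either side) |
|---|---|---|
| 0 | 100% | 100% |
| 7 | 50% | 75% |
| 14 | 0% | 50% |
| 30.4 | 0% | 0% |

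**Step 4. Total for the three strata (CT at 14 days).** Participants: 16 + 16 + 14 = 46. Planned assessments: 46 × 6 = 276.

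- Lag 0: 46 × 1 = 46 in the entry window, 46/276 = 16.7%.
- Lag 7: 46 × 0.5 = 23, 23/276 = 8.3%.
- Lag 14 or more: 0.

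**Step 5. Can one person meet both ND and CT?** Take ND as days 14 to 28 after diagnosis and a first treatment starting on day s. With CT as the 14 days after the start, the shared time is max(0, min(28, s + 14) − max(14, s)).

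- s = 7: min(28, 21) − max(14, 7) = 7 days.
- s = 14: 28 − 14 = 14 days.
- s = 21: 28 − 21 = 7 days.
- s = 0 or s = 28: 0 days.

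With CT as two weeks either side, time is shared for any s strictly between day 0 and day 42. Double membership is therefore possible where a first start counts towards the treatment stage (Introduction, Section 2.5). Under the Table 1 label it does not arise for first treatments. How many participants it would involve cannot be derived, because the article gives no timing of first treatment.

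**The case against.** The strongest reply is that a fixed group per person is the natural reading. The stages are recruitment strata, the ANOVA is between groups, and a growth model by group presupposes stable membership. On that reading the groups are the planned 16/16/14/14, the question is coherent, and only one word is wrong. The coding of groups could also be left to the full protocol. No decision rests on this exploratory analysis.

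Much of this stands. The fixed-group reading is workable, and the fix adopts it. But the article states the question in terms of current stage, and following that text would present entry-stage differences as current-stage differences. That is a misstatement, not an omitted detail.

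Three stronger inferences are tempting but not supported:

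- *No ND or ET participant is in the window at any of T1–T6.* This is established from T2 on. At T1 it depends on the unstated lag and ranges from 100% to 0%.
- *The ND/CT overlap affects 32 of 60 participants.* That figure is only 16 + 16, the sum of two strata. A CT participant changing therapy, as in the Introduction's own example, need not be newly diagnosed.
- *The ANOVA cannot be run because the definitions overlap.* ANOVA needs each participant in one group, and Table 1 provides one cell each. What the article lacks is the rule for someone who qualifies for two.

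Modelling actual stage as time-varying is also a weak remedy. Unless participants enter new windows, that covariate would mostly read as no stage, and treatment dates are not among the record items listed in Section 2.4.

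**Conclusion.** The concern holds in a limited form. As scheduled, at most one of six assessments per ND, CT or ET participant can fall in the entry window. That is at most 46 of 276 planned assessments (16.7%), and none if T1 is 14 or more days after entry with CT read as 14 days. The analysis therefore describes stage at enrolment and cannot support conclusions about current stage.

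The T2–T6 result rests on recruitment within the window and monthly spacing of about 30.4 days. The T1 result also depends on the lag and on how CT is read. Nothing is claimed for PT. The treatment stage is described inconsistently, and this needs reconciling; its numerical effect is unknown.

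The consequence is confined to an exploratory analysis. The feasibility endpoint, its success rule and the acceptability endpoint are untouched.

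**What to change.** 1. In Section 2.5, replace current stage with stage at enrolment (the Table 1 stratum) for both the ANOVA and the growth model, and limit the conclusions to that.
2. Add a between-stage comparison on the T0 PHQ-8 and GAD-7 as the exploratory test of whether distress differs by current stage. Table 2 already schedules these, and T0 is the assessment closest to the recruitment window. State that it uses the questionnaires and not the tool score, so it complements the tool-based analysis and does not replace it.
3. Reconcile the Introduction and Section 2.5 with the Table 1 label for the treatment stage. State one assignment rule for a participant who meets both the ND and CT definitions, so that each participant is in one group for both recruitment and analysis.

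The cost is a wording change, one assignment rule and one extra exploratory comparison. No new visits, measures or participants are needed.
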